### Study design

2.1

This single-blind, randomized controlled trial (ChiCTR2400093397, www.chictr.org.cn) employs a two-arm parallel design, consisting of an intervention group receiving a combination of VRCT, TCT, and PE, and a waitlist control group who will receive no training during the research period. As compensation, the waitlist group will be offered the same training after the follow-up assessment. All participants will undergo comprehensive assessments at four time points: baseline (week 0), mid-intervention (week 6), post-intervention (week 12), and a 12-week follow-up (week 24). The trial is designed in accordance with the CONSORT (Consolidated Standards of Reporting Trials) guidelines and will be conducted and reported accordingly.

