### Randomization and blinding

2.3

Participants will be randomly assigned in a 1:1 ratio to either the intervention group or the waitlist group using a computer-generated randomization sequence. To ensure baseline balance, randomization will be stratified by MCI subtype (amnestic vs. non-amnestic), baseline MoCA score (19–22 vs. 23–26), and age (60–65, 66–70, or 71–80 years). This approach ensures allocation concealment and minimizes selection bias. Due to the practical challenges of blinding participants, the study was conducted as a single-blind randomized controlled trial. Group allocation was concealed from partial research personnel—including outcome raters and data analysts—with the exception of the therapists administering the interventions, in order to reduce observer bias. All raters are explicitly prohibited from inquiring about participants’ group assignments, and all participants are instructed not to voluntarily disclose their treatment experiences or subjective impressions to raters.

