### Biological data acquisition

2.6

Biological data will be collected at three time points: baseline, trial completion (week 12), and 12-week follow-up (week 24). MRI scans will be acquired using a 3.0T Siemens Skyra scanner (Erlangen, Germany) at Zigong Mental Health Center. The data to be analyzed will include gray matter volume, cortical thickness, amplitude of low-frequency fluctuations (ALFF), bilateral hippocampal connectivity, posterior cingulate cortex (PCC) functional connectivity, default mode network (DMN) connectivity, and frontal network connectivity. Additionally, blood samples will undergo metabolomic analysis using mass spectrometry, while fecal samples will be analyzed for microbiome changes via 16S rRNA gene sequencing. All laboratory procedures will follow standardized protocols.

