**FIGURE 1 F1:**
[figure not shown]
Consolidated Standards of Reporting Trials (CONSORT) diagram.

**TABLE 3 T3:** Outline of study assessments and timelines.

Items	Screening	Week 0 (baseline)	Week 6 (mid-intervention)	Week12 (post-intervention)	Week 24 (12-week follow-up)
Informed consent	–	×	–	–	–
Randomization	–	×	–	–	–
Demographic information	–	×	–	–	–
Food diary	–	×	–	×	×
AD8	×	–	×	×	×
ISI	×	–	×	×	×
PHQ9	×	–	×	×	×
GAD7	×	–	×	×	×
AVLT	–	×	×	×	×
TMT (A and B)	–	×	×	×	×
DST (forward and backward)	–	×	×	×	×
MMSE	×	–	×	×	×
MOCA	×	–	×	×	×
ADL	–	×	×	×	×
IADL	–	×	×	×	×
GSRS	–	×	×	×	×
WHOQOL-OLD	–	×	×	×	×
Blood sample collection	–	×	–	×	×
Fecal sample collection	–	×	–	×	×
Magnetic resonance imaging (MRI)	–	×	–	×	×

AD8, Alzheimer’s Disease 8-item scale; ISI, Insomnia Severity Index; PHQ-9, Patient Health Questionnaire-9; GAD-7, Generalized Anxiety Disorder 7-item scale; MMSE, Mini-Mental State Examination; MOCA, Montreal Cognitive Assessment; ADL, Activities of Daily Living scale; IADLs, Instrumental Activities of Daily Living scale; GSRS, Gastrointestinal Symptom Rating Scale; WHOQOL-OLD, World Health Organization Quality of Life Instrument–Older Adults Module; AVLT, Chinese Auditory Verbal Learning Test; TMT (A and B), Trail Making Test (Parts A and B); DST, Digit Span Test (forward and backward).

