#### Statistical considerations

2.8.2

The analysis will adhere to the eHealth Consolidated Standards of Reporting Trials (CONSORT) criteria (Eysenbach, 2011), follow the intention-to-treat principle and per protocol set. The per-protocol set included participants who attended at least 70% of the assigned intervention sessions and completed all protocol-specified assessments (Zhang et al., 2018). Statistical analyses will be conducted using IBM SPSS Statistics (Version 24.0; IBM Corp., Armonk, NY, United States). Continuous variables are presented as mean and standard deviation; categorical variables as frequency and percentages.

For baseline characteristics, continuous variables are compared between groups using *t*-test, while categorical variables are analyzed using chi-square test. Primary outcomes will be analyzed using two-way repeated-measures ANOVA, evaluating the main effects of group, time, and their interaction. *Post-hoc* pairwise comparisons were conducted with Bonferroni correction for multiple comparisons. Missing follow-up data will be imputed using the last observation carried forward (LOCF) method. Sensitivity analyses (completers-only and per-protocol) will assess potential bias due to dropouts and imputation methods. We will also compare baseline characteristics between participants who dropped out and those who completed the study. All tests are two-sided, with statistical significance defined as *p* < 0.05.

Multimodal neurobiological correlates of treatment response will be assessed by integrating structural/functional MRI, gut microbiome, and plasma metabolome with behavioral outcomes. For analyses involving gut microbiota, key dietary patterns extracted from the 3-day food diaries will be included as covariates to enhance the validity of the findings. Hypothesis-driven analyses will include: (i) partial least squares (PLS) regression to identify multivariate brain-behavior associations, (ii) mixed-effects modeling for longitudinal effects, and (iii) mediation analysis to test whether brain-gut axis changes drive clinical improvement. Significance thresholds will be adjusted via Holm-Bonferroni correction.

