## Discussion

3

This study aims to (1) evaluate the efficacy of adjunctive VRCT in improving cognitive function in MCI, and (2) investigate potential brain-gut axis mechanisms mediating intervention effects through multimodal biomarker analyses.

Virtual reality cognitive training, as a demand-adapted cognitive training approach, offers an effective alternative that addresses several limitations of TCT, such as its time-consuming and labor-intensive nature (De Luca et al., 2020). Previous studies have suggested that VRCT may help delay or prevent dementia in high-risk middle-aged populations (Doniger et al., 2018). This effect is thought to stem from its capacity to enhance cognitive reserve and promote neuroplasticity (Teo et al., 2016). Furthermore, VRCT provides immersive and interactive experiences by simulating real-world environments, effectively integrating cognitive and physical training components (Stone et al., 2011). We hypothesize that this unique feature may compensate for the limitations of TCT and enhance its efficacy.

Recent evidences suggest that cognitive impairment is associated with specific gut microbial communities (Aljumaah et al., 2022; Kesika et al., 2021; Tooley, 2020). This finding suggests that cognitive decline may be improved through interventions such as probiotics, prebiotics, and commensal bacteria. Indeed, a recent meta-analysis indicates that probiotic supplementation may enhance cognitive function, particularly among individuals with MCI (Zhu et al., 2021). Moreover, brain imaging studies have provided evidence that gut microbiota are associated with alterations in brain structure and function (Tooley, 2020), further supporting their relationship with cognition. However, although cognitive training has been shown to improve cognition, few studies have explored its role in influencing the brain-gut axis. We hypothesize that adjunctive VRCT may mediate cognitive improvement in patients with MCI by influencing gut microbial composition, metabolic profiles, and brain function and structure. However, this hypothesis remains inconclusive. To explore potential neurobiological associations, we will collect multimodal data, including MRI, serum metabolomics, gut microbiomics, and comprehensive cognitive assessments.

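### The mediation analysis is given a causal reading (brain-gut changes *drive* improvement) that randomising the package alone cannot support; a within-arm common cause can give a positive test with no mediation

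*Protocol article*

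**What the plan says.** Section 2.8.2 (Statistical considerations) introduces the mechanistic work as follows: "Hypothesis-driven analyses will include: (i) partial least squares (PLS) regression to identify multivariate brain-behavior associations". Mixed-effects modelling comes second and, third, a "mediation analysis to test whether brain-gut axis changes drive clinical improvement". Thresholds are to be Holm-Bonferroni adjusted. Dietary patterns are covariates for the gut microbiota analyses; no other covariate is named for this block. The Discussion restates the second study aim as to "investigate potential brain-gut axis mechanisms mediating intervention effects through multimodal biomarker analyses".

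On timing, section 2.6 says: "Biological data will be collected at three time points: baseline, trial completion (week 12), and 12-week follow-up (week 24"). Table 3 agrees: stool, blood and MRI are taken at weeks 0, 12 and 24, and the tests that form the cognitive composite at weeks 0, 6, 12 and 24.

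On what is randomised, section 2.3 says: "Participants will be randomly assigned in a 1:1 ratio to either the intervention group or the waitlist group". Section 2.1 describes the arms as "an intervention group receiving a combination of VRCT, TCT, and PE, and a waitlist control group who will receive no training".

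Other parts are more cautious. The abstract expects preliminary evidence only. The Introduction and section 2.5 class the brain-gut work as exploratory. The Discussion calls the mediating hypothesis inconclusive and speaks of associations. The limitations concede that exercise intensity may vary between individuals and say that comorbidities will be examined as potential confounders, without linking either to the mediation analysis.

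**The concern.** A mediation analysis has two links: treatment to mediator, and mediator to outcome given treatment. Randomisation protects the first and the total effect. It does not protect the second, because participants are not randomised to a microbiota profile or a connectivity pattern. Within an arm, those whose biology changed more may differ from the others in ways that also affect cognition. One candidate is in the document: variation in exercise intensity among people who all attend the same dance sessions. Adjusting for diet does not address it.

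Timing adds to this. With no biology at week 6, no mediator is observed during treatment, so the data cannot show that biology moved before end-of-treatment cognition did.

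At stake is the mechanistic conclusion. Read as section 2.8.2 is worded, a significant indirect effect would be reported as evidence that gut or brain changes cause the cognitive benefit, when the design shows only that the pattern is compatible with it. The primary comparison, the sample size and the safety analysis are not affected.

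**Working it through.** **The plan's own figures.** The article gives no power figure for mediation, so there is none to reproduce. The sample sizes below are those of section 2.8.1: 46 required and 66 enrolled. The second follows from the first: 46 / (1 − 0.30) = 65.7, rounded up to 66.

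**Assumed inputs (the documents give none).** Treatment shifts the mediator M and cognition Y by d within-arm SDs each, with d = 0.5 or 0.8. The within-arm residual correlation of M and Y is r. The test is joint significance: the T coefficient in M on T, and the M coefficient in Y on T and M, both at two-sided 0.05. This is one mediator with no multiplicity correction.

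**Step 1: why the two explanations look alike.**
- Common cause, no mediation: M = dT + e, Y = dT + u, corr(e, u) = r. Regressing Y on T and M gives an M coefficient of r and a T coefficient of d − rd.
- True mediation with path r: M = dT + e, Y = (d − rd)T + rM + error with variance 1 − r².

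These give the same joint distribution of T, M and Y. With r = 0.3, the apparent indirect effect is 0.3d and the apparent share mediated is 30%, although the true share in the first case is 0%. No sample size separates them.

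**Step 2: how often the test is positive (n = 66, d = 0.5, r = 0.3).**
- Treatment to M: noncentrality d√n / 2 = 0.5 × 8.124 / 2 = 2.03, 64 df, power 0.516.
- M to Y given T: noncentrality about r√(n − 2) / √(1 − r²) = 0.3 × 8 / 0.954 = 2.52, 63 df, power 0.70.
- Both: 0.516 × 0.70 = 0.36. Simulation gives 0.35.

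**Step 3: simulated rates at unadjusted 0.05.**

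| n | d | No mediation, r = 0.3 | True mediation, path 0.3 | No mediation, r = 0 |
|---|---|---|---|---|
| 66 | 0.5 | 35% | 35% | 2% |
| 66 | 0.8 | 61% | 62% | 4% |
| 46 | 0.5 | 20% | 20% | 2% |

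The middle columns agree because of step 1; small differences are simulation error. Over r = 0.2 to 0.5 and both values of d, the no-mediation rate runs from 18% to 89% at n = 66 and from 10% to 72% at n = 46.

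**Step 4: reverse order.** If treatment improves cognition and cognition then alters biology (path 0.5), the test is positive in 17% of trials at n = 66 and d = 0.5.

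**Step 5: multiplicity.** At a threshold of 0.005 (a first Holm step among ten tests, 0.05 / 10; the number of tests is assumed), the 35% at n = 66 and d = 0.5 falls to 6 to 7%. The correction lowers how often a spurious result appears. It lowers the true-mediation rate equally, so it does not help tell the two apart.

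**Step 6: a lagged model.** Regress week-24 cognition on week-12 biology, adjusting for week-12 cognition (assumed test-retest correlation 0.7, stable common cause 0.3, n = 66). Positives are 10% without and 9% with mediation at d = 0.5, and 17% and 16% at d = 0.8. It restores time order but has little power, and it still does not separate the scenarios.

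**The case against.** The strongest reply is that this is one strong verb in an exploratory analysis. Five parts of it deserve an answer.

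- *The plan fixes no same-visit model.* This stands. A reader might infer that week-12 biology will be tested against week-12 cognition, but section 2.8.2 names no mediator visit, outcome visit or model. The schedule also allows week-12 biology with week-24 cognition. Such detail may sit in a full protocol or SAP not shown, and its absence is not the point here.
- *Mediation can be told from parallel response.* This stands in part. If treatment moves biology and cognition independently within arms, the test is positive in only 2 to 5% of trials. A uniform effect of exercise on both is a direct effect that the treatment term already absorbs. The difficulty needs within-arm correlation from another source.
- *Multiplicity is controlled.* This stands as to frequency (step 5), not as to interpretation.
- *Nothing would be declared met.* This stands. A reader might infer that the mechanistic objective would be claimed as achieved, but the article sets no success criterion for it and hedges in several places.
- *Any trial with an unrandomised mediator has this limit.* This is true, and it is why the conclusion attached to the test should be worded accordingly. The cautious passages elsewhere do not withdraw the causal aim in the statistics section, and the limitations do not mention the problem. No SAP can randomise the mediator or supply biology at a visit where none is collected.

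**Conclusion.** The point holds as a limit on interpretation. Section 2.8.2 attaches a causal conclusion to a test whose second link the design does not identify, and names only diet as a covariate, for part of the analyses. Under an assumed residual correlation of 0.3 and an effect of 0.5 SD on both, about 35% of trials of 66 would be positive with no mediation at unadjusted 0.05. The rate is 2 to 5% if that correlation is zero, and lower in either case after Holm-Bonferroni correction. Effect sizes and correlations are assumptions throughout; the conclusion rests on what is randomised and on the equivalence in step 1, not on any one percentage.

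Two stronger readings are not supported. The documents do not show that a positive result is likely to be false, since the within-arm correlation is unknown. Nor can it be said that a lagged model would cure the problem: it does not remove confounding, and if week-12 cognition is a covariate it addresses only later change.

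**What to change.** In section 2.8.2 of the protocol, or in the SAP:

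1. Replace *drive* with *are statistically consistent with mediating*, and label the mediation result exploratory and associational. Align the second aim in the Discussion.
2. Adjust the outcome model for baseline mediator, baseline composite and the stratification factors (MCI subtype, baseline MoCA band, age band), in addition to diet for the gut analyses.
3. Add a sensitivity analysis that reports how large a mediator-outcome residual correlation would remove the indirect effect. In the simple linear model above this is the within-arm correlation itself (0.3 in the example), so readers can judge whether a common cause of that strength is plausible.
4. Optionally, report a model of week-12 biology on week-24 cognition as supportive. Use observed week-24 scores: the LOCF imputation planned in the same section would carry earlier cognition forward for dropouts and undo the time order. State its low power, and that it does not remove confounding.

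The cost is slightly more analysis work and a more modest mechanistic conclusion. No new visits, samples or participants are needed.

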#### Safety analysis

2.8.3

Safety considerations will be a priority throughout the study. All adverse events (AEs) will be carefully documented. AEs are defined as any unfavorable or unintended sign, symptom, or disease temporally associated with the study intervention. Special attention will be paid to VR-related discomfort (e.g., dizziness, nausea, eyestrain, and headache). AEs will be systematically queried and recorded immediately after each training session. Vital signs (blood pressure and heart rate) will be monitored immediately after each training session. All AEs will be graded for severity based on participant self-report, using the following criteria: Mild (easily tolerated), Moderate (interferes with usual activities), or Severe (incapacitating). To comprehensively evaluate the safety profile, the incidence and severity distribution of adverse events will be analyzed using descriptive statistics for all randomized participants.

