**Methods:**

This study is a randomized single-blind controlled trial that will include 66 older adults with MCI from the community. Eligible participants will be randomly assigned in a 1:1 ratio to the intervention group or the waitlist group. The intervention group will complete 36 sessions (three sessions per week for 12 weeks) consisting of virtual reality cognitive training (VRCT), traditional cognitive training (TCT), and physical exercise (PE). The control group will not receive any intervention during the study period. The primary outcome is the change in a memory-weighted cognitive composite score. Exploratory outcomes: mechanistic changes along the brain-gut axis, including: (1) Changes in gut microbiota alpha/beta diversity and composition assessed by 16S rRNA gene sequencing, (2) Changes in resting-state brain activity and functional connectivity assessed by fMRI. Outcome measures will be assessed at three or four time points: baseline, mid-intervention (Week 6), post-intervention (Week 12), and at a 12-week follow-up (Week 24).

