Exploratory outcomes include the following: (1) Changes in gut microbiota alpha/beta diversity and composition assessed by 16S rRNA gene sequencing, (2) Changes in resting-state brain activity and functional connectivity assessed by fMRI. (3) changes in serum metabolites, evaluated via metabolomic analysis; (4) changes in sleep quality, measured by the Insomnia Severity Index (ISI); (5) changes in mood, assessed using the Patient Health Questionnaire-9 (PHQ-9) and the Generalized Anxiety Disorder-7 (GAD-7) scales; (6) changes in daily living abilities, measured by the Instrumental Activities of Daily Living (IADL) and Activities of Daily Living (ADL) scales; (7) changes in gastrointestinal symptoms, assessed using the Gastrointestinal Symptom Rating Scale (GSRS); (8) changes in quality of life, measured by the WHO Quality of Life-OLD (WHOQOL-OLD) scale.

Safety evaluation will include the incidence and severity of all adverse events (AEs), with particular attention to VR-related discomfort (e.g., dizziness, nausea, eyestrain, headache). AEs will be systematically recorded after each training session, and vital signs (blood pressure, heart rate) will be monitored immediately post-session. All AEs will be graded as mild, moderate, or severe based on participant self-report.

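### Adverse events are solicited only after training sessions, which the waitlist arm does not have, yet are summarised for all randomised participants, so the arms cannot be compared on harms

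*Protocol article*

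**What the plan says.** Two sections describe how AEs are collected, and both name the same trigger. Outcome measurements (2.5): "AEs will be systematically recorded after each training session, and vital signs (blood pressure, heart rate) will be monitored immediately post-session". Safety analysis (2.8.3): "AEs will be systematically queried and recorded immediately after each training session".

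The definition is also in 2.8.3: "AEs are defined as any unfavorable or unintended sign, symptom, or disease temporally associated with the study intervention". The same section opens with a general statement, "All adverse events (AEs) will be carefully documented", and closes with the analysis: "the incidence and severity distribution of adverse events will be analyzed using descriptive statistics for all randomized participants".

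On exposure, the Abstract states: "The control group will not receive any intervention during the study period". Study design (2.1) and Procedure (2.7) agree, and offer the waitlist arm the training only once the follow-up assessment at week 24 is done. Both arms attend weeks 6, 12 and 24 (2.1, Table 3).

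**The concern.** Collection, definition and analysis set do not fit together. The analysis set includes both arms. The only stated occasion for asking about AEs exists in one arm, and the definition refers to something that only that arm receives. A control participant with headache or dizziness at week 8 has no stated occasion to be asked about it. Read literally, the event would not meet the definition either.

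What is at stake is the use of the control arm for harms. The symptoms singled out in 2.8.3 (dizziness, nausea, eyestrain, headache) are not specific to VR, and the Discussion accepts that comorbid conditions may influence outcomes in these older participants. A concurrent control arm questioned in the same way is what would separate background symptoms from those due to the package. The trial has the arm but does not question it. A later statistical analysis plan cannot repair this, because events that were never asked about cannot be recovered reliably at analysis.

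**Working it through.** **Inputs from the article**
- Enrolment is 66 (Sample size, 2.8.1). Check: 46 / (1 − 0.30) = 65.7, rounded up to 66.
- Allocation is 1:1 (2.3), so 66 / 2 = 33 per arm if exactly balanced.
- Sessions: 3 per week × 12 weeks = 36 in the intervention arm, 0 in the waitlist arm.
- No AE rate is given. The counts below are assumptions, from about 10% to 50% of the trained arm.

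**Solicited occasions per participant**

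| Period | Intervention | Waitlist |
|---|---|---|
| Weeks 0–12 | 36 | 0 |
| Weeks 12–24 | none stated | none stated |

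**Display A: pooled over all randomised.** Let x be the number of trained participants with an event, and let none be recorded among controls. The reported incidence is x/66, while the incidence among the trained is x/33. The ratio is 33/66 = 0.5 whatever x is.

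| x | Among the trained, x/33 | Reported, x/66 |
|---|---|---|
| 3 | 9.1% | 4.5% |
| 7 | 21.2% | 10.6% |
| 10 | 30.3% | 15.2% |
| 16 | 48.5% | 24.2% |

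**Display B: by arm.** Let c be the true number of controls with an event, none of it recorded. The true difference is (x − c)/33 and the reported difference is x/33, so the excess is overstated by c/33, the whole unrecorded background rate.
- x = 7, c = 7 (no excess harm): the true difference is 0. The table reads 21.2% against about 0%, a false difference of 21.2 percentage points.
- x = 10, c = 7: the true difference is 3/33 = 9.1 points. The table reads 30.3% against about 0%, so the difference is overstated by 7/33 = 21.2 points.

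The two displays err in opposite directions. A understates the rate among the exposed. B leaves that rate undiluted but overstates the excess over control.

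**The case against.** Several points on the other side are fair.

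- **The display is not stated.** Naming all randomised participants fixes the population, not the layout. A reader might infer that harms are both diluted and set against a zero control column. Those are consequences of alternative displays, and the article commits to neither. This stands.
- **Zero is not a rule.** A reader might also infer that controls will show exactly 0/33 whatever happens. The general promise to document all AEs does not exclude events that controls volunteer at visits, so near zero by design is as far as the text goes. This stands, but it does not rescue the comparison: no route for controls is described, and volunteered reports are not comparable with 36 solicited queries.
- **A journal article condenses, and Table 3 is not a full safety schedule.** Table 3 has no AE row, but it also omits the session-level AE and vital-sign recording that the text requires, so the missing row proves little. This stands. The point rests instead on what 2.5 and 2.8.3 do state: the same trigger twice, and a definition tied to the intervention.
- **Some symptom data exist in both arms.** The GSRS, ISI, PHQ-9 and GAD-7 are given at weeks 6, 12 and 24. They inform gastrointestinal symptoms, sleep and mood, but do not replace AE collection for dizziness, eyestrain or headache.
- **Post-session questioning suits VR discomfort.** It does, and it should stay. It cannot say how much of the same symptoms would occur without training.
- **Background rates are not documented.** A reader might assert that dizziness or falls are common at this age without training. The article gives no such rate, so the argument does not use one. The background counts above are illustrations.

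**Conclusion.** The concern holds in this form: AEs are solicited only at training sessions and defined relative to the intervention, yet are summarised for all randomised participants. The arms therefore cannot be compared on harms. If incidence is pooled, the rate among the trained is roughly halved. If it is shown by arm, any excess is overstated by whatever background goes unrecorded in controls.

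The sizes rest on 33 per arm, on assumed event counts, on events in the trained arm being captured, and on few or no volunteered reports from controls. The safety analysis is descriptive, with no test or safety hypothesis, so no error rate and no efficacy conclusion is affected. The change should be made before more data accrue, but the trial's main question does not depend on it.

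**What to change.** 1. In 2.8.3, define an AE as any untoward event after randomisation, and record relatedness to the intervention as a separate field.
2. Ask both arms the same AE questions at weeks 6, 12 and 24, and add the row to Table 3. This also covers weeks 12 to 24 in the intervention arm.
3. Protect the blinding. Section 2.3 bars raters from asking about allocation and tells participants not to describe their treatment experience to them. A self-completed form withheld from the outcome raters meets both conditions.
4. Report AEs by arm from these common visits.
5. Keep the post-session questions, and report session-elicited VR discomfort separately, with participants who had at least one VR session as the denominator.

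The cost is a short form at three visits that already take place, a wording change, and care in handling the form so that raters do not see it. No extra visit is needed.

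### Severity of every adverse event rests on participant self-report of tolerability and function, so a symptom-free sign can only be graded mild

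*Protocol article*

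**What the plan says.** The Safety analysis section (2.8.3) sets a broad scope: "AEs are defined as any unfavorable or unintended sign, symptom, or disease temporally associated with the study intervention". It separates capture from grading. On capture it says "All adverse events (AEs) will be carefully documented" and "AEs will be systematically queried and recorded immediately after each training session". It also plans objective measurement: "Vital signs (blood pressure and heart rate) will be monitored immediately after each training session".

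On grading it gives one rule for every event: "All AEs will be graded for severity based on participant self-report, using the following criteria". The levels are "Mild (easily tolerated), Moderate (interferes with usual activities), or Severe (incapacitating". The Outcome measurements section (2.5) repeats the rule: "All AEs will be graded as mild, moderate, or severe based on participant self-report". Neither section names a second source for the grade or a criterion for grading a sign.

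Section 2.8.3 then makes the grades part of the safety result. The frequency of adverse events and their spread over the severity levels are to be described for all randomized participants.

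**The concern.** The grading rule is narrower than the definition that it serves. Self-report of tolerability and function suits a symptom. It does not suit a sign that the participant cannot feel, because there is no experience to report. The article nevertheless applies the rule to all adverse events, in two places.

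The safety setting makes this more than a matter of wording. Participants are 60 to 80 years old (section 2.2), they exercise to a heart-rate target three times a week (section 2.4.1), and the Discussion acknowledges possible comorbid conditions. Blood pressure and heart rate are relevant safety measurements here, and the trial takes them after each session. What is at stake is how the severity table can be read. A low share of moderate and severe events could partly reflect the rule and not what happened.

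**Working it through.** The article states no figure on this point, so there is nothing to reproduce. The check sets the definition, the capture rule and the grading rule side by side, and applies the grading rule to each kind of event in the definition.

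1. **Scope.** The definition in 2.8.3 names three kinds of event: sign, symptom and disease.
2. **Capture.** All adverse events are to be documented, and they are queried and recorded after each session. Nothing limits capture to what the participant reports, and vital signs are measured separately.
3. **Grading.** The rule covers all adverse events, its source is participant self-report, and its levels are easily tolerated, interfering with usual activities, or incapacitating.

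Applying step 3 to step 1:

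- *Symptom* (for example dizziness or nausea during VR). The participant can say how well it was tolerated and whether it interfered. All three levels are reachable, so the rule works.
- *Disease with functional impact.* The participant can report how it affects daily activities. The rule works.
- *Sign without symptoms* (for example an abnormal post-session blood pressure that is not felt). The participant reports no interference, which rules out moderate, and no incapacity, which rules out severe. Only mild remains. Two readings of very different size get the same grade, because size does not enter the rule.

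The gap is therefore confined to events that the participant does not feel. Within that group any error runs one way, towards mild.

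**Effect on the reported result.** Let N be the number of recorded adverse events, and a the number graded moderate or severe. Let k be the number that are symptom-free signs, and m (between 0 and k) the number of those that a criterion based on the sign itself would place above mild.

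- Share above mild under the stated rule: a / N.
- Share above mild if signs were graded on their own criteria: (a + m) / N.
- Shortfall: m / N, which lies between 0 and k / N.

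The article gives no N, k or m, so the shortfall cannot be given a value.

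**How many readings are planned.** With 66 participants randomized 1:1, the intervention arm has 66 / 2 = 33. At 36 sessions each, the planned post-session readings number at most 33 × 36 = 1,188, assuming full attendance and no dropout. This counts measurement occasions. It does not estimate how many would be adverse events or how many would be misgraded.

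**The case against.** The strongest reply is that the scale is consistent with itself. It measures severity as tolerability and functional impact, and on that construct a sign that limits nothing is mild. Grading by the size of the sign would be a different construct, and choosing between the two is a design decision. This stands in part: the grade is a valid record of felt burden. But the result is to be reported as the severity of all adverse events, signs included, and for unfelt signs the grade carries no information on how large the abnormality was.

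A second reply is that a journal article condenses the full protocol, which may say more. That covers what is left out, such as how an abnormal reading becomes an adverse event. It does not cover a rule that the article states twice, for all events, and that does not fit part of its own scope.

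A third reply is that self-report is the natural source for the events singled out, which are dizziness, nausea, eyestrain and headache. Participants must have an MMSE of at least 24, and they are asked straight after each session. This is right, and it is why participant ratings of VR discomfort should be kept.

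A reader might infer more than the article supports:

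- *Symptom-free events go unrecorded.* The article says that all adverse events are documented, and self-report governs only the grade.
- *Clinicians are excluded, or participants grade their own events by reporting to the treating therapist.* The article names self-report as the basis of the grade. It does not say who queries events or who assigns the grade, and it does not rule out clinical review.
- *The vital signs feed no analysis.* Vital-sign monitoring is listed in 2.5 under the safety evaluation. How the readings are summarised may be left to a fuller document.
- *The 1,188 readings measure the bias.* They only count planned occasions.

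**Conclusion.** The point holds for severity grading only. As written in 2.5 and 2.8.3, the rule can grade a symptom-free sign only as mild, whatever its size, so the reported severity distribution can understate such events. The direction is clear from the text. The amount is unknown and would be zero if no such event occurred, or if none would rank above mild on criteria of its own.

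The conclusion assumes that the grading rule is applied as stated and that no fuller document adds another basis for grading signs. The safety analysis is descriptive, so no hypothesis test, significance level, sample size or efficacy conclusion depends on this. It is worth correcting because the rule is explicit, the conflict lies within one section, and the correction is cheap.

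**What to change.** Reconcile the grading rule with the adverse event definition in both 2.5 and 2.8.3:

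- State that an investigator already on the study assigns the severity grade of each adverse event.
- For symptoms, keep the participant's report as the input to that grade.
- For signs, use criteria that the investigators fix in advance. Their content is for the investigators to decide.
- Report participant-rated VR discomfort separately, so that the participants' own experience remains visible.

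Grades are assigned as events occur, and the Procedure section describes recruitment as under way. The change is best made before more events are graded, and the report should say from when it applied. The cost is revised wording in two sections, a field on the adverse event form and a little investigator review time.
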